### **5.3 Study Endpoints**

#### **5.3.1 Primary clinical Endpoint**

**Depression, negative affect and wellbeing:**

|                            | Objective | Self-report |
|----------------------------|------------------|--------------------|
| Depression/negative affect | IDS interview    | DASS               |
| Positive affect/wellbeing  |                  | PANAS, WBS         |

Inventory of Depressive Symptomatology- Clinician Rated (IDS-C30) (Rush et al., 1986; Rush et al., 1996)

The Depression, Anxiety Stress Scale (DASS) (Brown et al., 1997; Crawford & Henry, 2003; Lovibond & Lovibond, 1995)

Positive and Negative Affect Schedule – Expanded Form (PANAS-X ) (Watson & Clark, 1994)

The Wellbeing Scale (WBS)(Ryff, 1989)

#### **5.3.2 Secondary Endpoints**

Attention, Emotion Regulation/Reactivity, and Wakefulness

| PFC Domain               | Objective          | Self-report |
|---------------------------------|---------------------------|--------------------|
| attention                       | SART errors               | FFMQ, MAAS         |
| emotional reactivity/regulation | EMG response to emotional | DERS, FFMQ, SCO    |

|             |                                   |     |
|-------------|-----------------------------------|-----|
|             | photos                            |     |
| wakefulness | 5-9 HZ EEG power
sleep latency | KSS |

### 5.3.3 Exploratory endpoints

Factors that are not meditation type, that may influence outcome, including:

- therapist-level factors include warmth/empathy; adherence
- Participant level factors include personality/temperament

## 6. STUDY POPULATION

### 6.1 Overview

***Human Subjects Involvement and Characteristics:*** Participants will complete a 6 month protocol including questionnaires, in lab assessments of attention, sleep propensity and emotion, 8 weeks of meditation training, and a 3 month follow-up interview. 105 participants will be enrolled from the general community ages (ages 18-65). The sample was chosen to represent the population that most frequently uses meditation based modalities, (i.e. "stressed" individuals with persistent mild to severe levels of depression, anxiety and negative affect.)

### 6.2 Inclusion Criteria:

Participants must meet the following requirements to participate in the study

- English-speaking
- ages 18-65
- mild-severe levels of depression (IDS 10-48) or high level of negative affect (PANAS negative affect scale >20 in last month).
- May include the following DSM diagnoses and classifications of emotional disturbances:  
296.xx Major Depressive Disorder, single episode or recurrent, chronic, or in partial remission;  
300.4 Dysthymic Disorder;  
311 Depressive Disorder NOS (minor depression and recurrent brief depressive disorder;  
300.2 Generalized Anxiety Disorder;  
293.84 Anxiety Disorder Due to a Medical Condition;  
300.00 Anxiety Disorder NOS.

### 6.3 Exclusion Criteria:

Participants will be excluded if they meet any one of the following:

At time of screening interview (past month)

- Extremely severe levels of depression (IDS>48)
- active suicidal ideation (IDS-18 >2)

- presence of Axis I personality disorder
- panic disorder
- post-traumatic stress disorder
- obsessive-compulsive disorder
- eating disorder, or substance abuse/dependence
- inability to read and write in English,
- current psychotherapy ( >1 mo)
- change in antidepressant medication type or dosage in the last 8 weeks.

Lifetime history exclusions:

- bipolar disorder
- psychotic disorders (cyclothymia, schizophrenia, schizoaffective disorder)
- persistent antisocial behavior or repeated self-harm,
- borderline personality disorder,
- organic brain damage
- regular meditation practice

Rationale: These participants are excluded because they may disrupt group participation, require additional or specialized treatment, are outside the range of meditation uses, are typically excluded from meditation studies and therefore not "representative", or may confound the results of the study.

## 6.4 Inclusion of Women and Minorities

Current census data indicate that the racial/ethnic breakdown of the state of Rhode Island is as follows: .3% of the population is American Indian or Alaskan Native, 1.0% is Asian, 4.5% is Black, 1.2% is Hawaiian/Pacific Islander, 8.4% is Hispanic/Latino, 80.7% is White, and 4% is some other ethnicity. While we expect that enrollment will represent these ratios, we will attempt to oversample minority participants to increase their representation in the sample to more closely match the racial and ethnic distribution of individuals living in the U.S. (75.1% White, 12.3% Black or African American, 3.6 % Asian, 0.9% American Indian/Alaska Native, 0.2% Native Hawaiian/Other Pacific Islander, 5.5% some other race, and 2.4% two or more races; 12.6% Hispanic/Latino and 87.4% Non-Hispanic/Latino. An effort will be made to enroll individuals of various ethnic and racial minority backgrounds by advertising in newspapers and clinics with a high minority clientele. [name], who is Director of the Multicultural Psychiatry Clinic at Butler, will consult on issues regarding the increased recruitment and retention of minority participants in the study.

Preliminary data suggest that females represent MBSR/MBCT study samples in a 3:2 ratio. Non-English speaking minorities will not be eligible for the study because the treatments will be delivered in English. Table 5 shows the number of study participants per ethnic/racial category to be enrolled based on Census data.

## 6.5 Inclusion of Children

Children under age 18 will not be eligible for the study because their inclusion would require age-appropriate adaptations to the treatments, and parental consent. Studies performed in our lab that include adolescents under 18 {[name], 2010 #15} required substantially shorter meditation times than older samples. In addition, the prefrontal cortex, which is a central target of this study, is not fully developed in children.

## 6.6 Target/Planned Enrollment

### Targeted/Planned Enrollment Table

**Study Title:** Dismantling Mindfulness: Contributions of Attention vs. Acceptance to the Treatment of Affective Disturbances

**Total Planned Enrollment:** 105

| TARGETED/PLANNED ENROLLMENT: Number of Subjects |                   |              |              |
|--------------------------------------------------------|-------------------|--------------|--------------|
| Ethnic Category                                 | Sex/Gender |              |              |
|                                                        | Females    | Males | Total |
| Hispanic or Latino                                     | 6                 | 3            | 9            |
| Not Hispanic or Latino                                 | 57                | 39           | 96           |
| Ethnic Category: Total of All Subjects *        | 63                | 42           | 105          |
| Racial Categories                               |                   |              |              |
| American Indian/Alaska Native                          | 0                 | 0            | 0            |
| Asian                                                  | 3                 | 2            | 5            |
| Native Hawaiian or Other Pacific Islander              | 1                 | 1            | 2            |
| Black or African American                              | 5                 | 3            | 8            |
| White                                                  | 54                | 36           | 90           |
| Racial Categories: Total of All Subjects *      | 63                | 42           | 105          |

\* The “Ethnic Category: Total of All Subjects” must be equal to the “Racial Categories: Total of All Subjects.”

## 6.7 Co-enrollment Guidelines

Study participants may not co-enroll in any other treatment studies.

Enrollment in non-invasive assessment-only studies may be permitted, but must be approved by the PI.

## 6.8 Strategies for Recruitment and Retention

**Recruitment:** The Principle Investigator and research staff will recruit participants from the local community through a variety of sources: posting informational flyers/brochures, placing print advertisements, making personal appearances at community events, distributing study information through primary care clinics, and posting e-advertisements on relevant websites.

**Retention:**

A recent 2 armed RCT of MBCT vs waitlist indicated a retention rate of 93% for the waitlist group and 78% for the waitlist. Since all three arms of this study are active treatments, we project a retention rate similar to the MBCXT study (>85%) for all arms.

Several strategies will be used to increase retention, with the target goal of keeping drop outs below 15%. First, patients will be asked to provide the names and phone numbers of multiple individuals who always know how to contact the participant. Participants will receive calendars about treatment and study schedules and reminder calls before important dates. They will also be followed up if they miss a class or assessment. Retention procedures will be reviewed regularly with the mentorship team and revised accordingly

## 7. METHODS FOR MINIMIZING BIAS

### 7.1 Treatment Randomization

#### 7.1.1 Background Rationale

Treatment randomization procedures have been discussed with mentors and are based on the following considerations:

#### 7.1.2 Clinical and Treatment Considerations

- Group size. Ideal MBCT groups size = 8-12 ([name]); groups should not be smaller than 4
- Wait time to treatment. Minimal wait time between baseline assessment, randomization and beginning of treatment

#### 7.1.3 Feasibility and practical considerations

- *Basic Calculations.* Because only one lab assessment can be done per day, with a reasonable goal of 1-4 per week, 4-16 subjects will be eligible for randomization in a given month. Given that an ideal class size is 8-12 (Max 16), with a minimum of 4, basic calculations yield enough participants for randomization into one treatment at a time,

with a range of 0-4 weeks wait time (Maximum 4 weeks) to enter treatment. This option would yield a minimal group size within 1 month, even if recruitment is extremely slow (1 per week). Alternatively, we would have to wait 3 months to get enough people to allocate into 3 simultaneous treatments, or have class sizes less than 4, which is unacceptable

- *Therapist and RA availability.* Since therapists are unpaid volunteers, they have agreed to run 1-2 groups per year each. Research Assistants are typically university students who operate on an academic year, and are less reliable during exams and holidays and transition periods.
- Based on previous research and as described in the Study Timeline section of the Research Strategy, we planned on 3 groups per year, 1 group each "season" (Fall, Spring, Summer) and gradually increasing our recruiting, assessment and therapist capabilities to 8-12 participants per group. Because of extended delays in the protocol review process, we expect to begin data collection about 12+ months behind schedule (Spring 2013).

### **7.1.4.2 Timing:**

Treatment programs are scheduled to start on Feb 15, June 1 and Sept 15 each year.

Randomization will occur no later than 3 days before the treatment start date. Randomization requires a quorum of at least 4 eligible participants who have completed baseline assessments. This will ensure adequate group size and minimize wait time to enter treatment.

### **7.1.4.3 Group Randomization**

Treatment randomization is performed at the group level, rather than the individual level. For example, each group of 4-16 participants will be randomly allocated into one of three treatments (i.e. group randomization) 9 different times.

**Stratification:** Stratification by baseline characteristic will not be used because it would delay treatment, and because it is not possible in group randomization designs. Group differences in baseline characteristics will be assessed (see [Preliminary Analyses section](#))

and if present, incorporated into analysis plan under the guidance of statistical mentors. Seasonal effects will be accounted for by balancing treatment equally over the 3 seasons (spring, Summer, fall).

**Masking:** The results of each treatment randomization will be recorded and communicated by an independent RA that is not involved in patient contact.

**Procedure:** An independent statistician, [name] PhD., at Brown Center for Statistical Sciences is responsible for generating random treatment randomization sequences. The results of each randomization will be recorded by the statistician and communicated to the PI who is one of the co-therapists for each treatment. The PI will maintain the treatment location information in a password-protected electronic file, and provide de-identified codes to signify different treatments during analysis.

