## 11.3 Analysis Plan:

### 11.3.1 Preliminary Analyses:

The purpose of the preliminary analysis is to investigate the data for patterns that may impact subsequent analyses, such as: group differences at baseline, differential attrition, compliance or instructor qualities, competence, adherence or ratings. Because we used a group randomization, we must also assess the degree to which group-ness influences outcome (i.e. intra-group correlation).

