### 11.3.2 Primary Analyses:

**To asses and compare the effects of FA and OM modules on clinical efficacy vs standard MBCT** Multilevel Modeling (MLM) will be used to compare the trajectories of clinical improvements in affective states (IDS, DASS PANAS, WBS) for each treatment.

Level 1 variables will include depression, negative affect and wellbeing scores at multiple time points.

Level 2 variables will include treatment type, meditation practice amount and demographic variables (age, sex, education). A MLM approach (Bryk & Raudenbush, 1992) was chosen for analysis because it is well suited to repeated measures designs, yields more information than ANOVAs (i.e. allows for individual growth curves), has the ability to retain missing cases, and fits my training goals of advanced statistical analysis skills for treatment research.

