### **11.3.3 Secondary Analysis:**

#### **11.3.3.1 To compare the effects of FA, OM and MBCT on attention, emotion regulation and wakefulness:**

A linear mixed model approach will be used to compare the effects of each treatment on each measure.

Type of treatment and time (baseline vs. post-intervention) will be modeled as fixed effects. In addition, variables identified in preliminary analysis will be added to the model as predictor variables or covariates.

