#### **11.3.3.2 To determine which neurobehavioral process drives the clinical benefits of mindfulness:**

I chose multiple regression because it can evaluate associations between clinical outcome and multiple correlated continuous and categorical variables (it also fits my training goal of increasing multivariate statistical knowledge). Multiple regression analyses will be conducted across all groups to maximize power and allow for between-treatment comparisons. Criterion variables will include clinical outcome measures of affective disturbance and wellbeing (IDS, DASS, PANAS, WBS) (baseline- 3 month follow-up change scores). Aggregate scores for 1) attention, 2) emotional reactivity/regulation and 3) wakefulness will be entered as separate predictors. Variables that are not equivalent at baseline but may impact outcomes (e.g. sex, education etc) will also be entered as predictor variables. Hypothesized interactions between wakefulness, attention and emotion regulation will be also evaluated using multiple regression.

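### Covariates added to the arm comparisons are picked by observed arm differences, including post-randomisation ones, instead of being fixed in advance on prognostic grounds

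*Protocol*

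**What the plan says.** Four places in the protocol bear on which covariates enter an arm comparison.

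- **7.1.4.3 Group Randomization.** Stratification is ruled out. Baseline differences between arms are to be assessed and, "if present, incorporated into analysis plan under the guidance of statistical mentors". No list, no threshold for a difference and no requirement of prognostic value is given.
- **11.3.1 Preliminary Analyses.** The screen looks for "group differences at baseline, differential attrition, compliance or instructor qualities, competence, adherence or ratings".
- **11.3.3.1 (secondary mixed models).** Treatment and time are fixed effects, and "variables identified in preliminary analysis will be added to the model as predictor variables or covariates". No covariate is named in advance, and the sentence is not limited to baseline variables.
- **11.3.2 Primary Analyses.** Here covariates are named: "Level 2 variables will include treatment type, meditation practice amount and demographic variables (age, sex, education".

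Section 11.3.3.2, the mechanism regression, has a different rule: "Variables that are not equivalent at baseline but may impact outcomes (e.g. sex, education etc) will also be entered as predictor variables".

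On the design, "Treatment randomization is performed at the group level, rather than the individual level", and the example given is that this happens "9 different times".

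**The concern.** Under proper randomisation, a baseline difference between arms is a chance event. Its size carries no information on whether the variable predicts the outcome. A rule that lets in what happens to differ will usually leave out a strong predictor that happens to balance, and will sometimes let in a variable of no use. With no threshold and no list, the final model is also open to choice once data are in hand.

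The second fault is more serious. Attrition, compliance, and ratings of how instructors delivered the class are observed after allocation and may be consequences of the assigned treatment. Adjusting an arm comparison for them can take out part of the effect being estimated, or distort it. The protocol itself treats arm differences in attrition and adherence as study questions (11.5) and low adherence as an outcome of interest (10.6.3.2). It should not also use them as adjustment terms. The same holds for meditation practice amount in the primary model.

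This falls where the trial expects most. Section 11.2 predicts the largest arm differences on mechanism, which are the models of 11.3.3.1. Sections 11.1 and 11.4.1 make estimation of treatment parameters for a larger trial the main product.

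**Working it through.** **The plan's own figure.** The protocol gives no figure for covariate selection. The only related number is the sample size, used below as a setting. With f = d/2 = 0.1675, N = 90, m = 2 measurements and an assumed correlation ρ = 0.5 between them (the protocol states none), λ = f²·N·m/(1−ρ) = 0.02806 × 90 × 2/0.5 = 10.1 on 2 and 87 df. This gives power of 80.5%, so 90 reproduces. The point does not depend on it.

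**1. How often the trigger fires.** Assume a .05 threshold and k independent characteristics with no true difference. The chance of at least one flag is 1 − 0.95^k.

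| k | Chance of at least one flag |
|---|---|
| 3 | 14% |
| 5 | 23% |
| 10 | 40% |
| 15 | 54% |

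These hold for an intraclass correlation (ICC) of 0. The threshold and the counts are assumptions.

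**2. What the rule does to the test.** Simulation inputs, from the protocol: 3 arms of 30 (11.4.4). Assumed: individual-level allocation, five standard normal candidate covariates of which one has correlation r with outcome, entry if the arm-difference p < .05, arm means 0, 0.3 and 0.6 SD, 2-df F test at .05, 5,000 runs. Where two figures are shown, they are from two separate runs.

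| r | Power, no covariate | Power, triggered rule | Power, prognostic covariate fixed |
|---|---|---|---|
| .3 | 51% | 50-51% | 55% |
| .5 | 52% | 50-52% | 64-65% |
| .7 | 52% | 52% | 81-82% |

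The prognostic covariate entered in only about 4% of trials, whatever its r, so the triggered rule performs like no adjustment at all. A fixed covariate cuts residual variance by the factor 1 − r², equivalent to multiplying the sample by 1/(1 − r²):

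- r = .3: 1/0.91 = 1.10
- r = .5: 1/0.75 = 1.33
- r = .7: 1/0.51 = 1.96

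**3. Type I error, same settings, no arm effect.** The triggered rule gave 4.7%, 4.2% and 3.6% at r = .3, .5 and .7 in one run and 3.8-4.4% in the other. The fixed covariate gave 5.0%. With nine classes of 10, a covariate ICC of .05 and r = .5, the triggered rule gave 4.9% and the fixed covariate 4.7%. The rule is at or below nominal throughout.

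**4. Class allocation.** With 3 arms × 3 classes × 10, a person-level ANOVA on a balanced characteristic rejects about 5%, 6% and 12-13% of the time at ICC 0, .01 and .05. All three ICCs are assumptions. The only documentary evidence, in 11.4.5.2, is that correlations for depression-related outcomes were all below .01. That does not settle the matter for baseline characteristics, but it gives no support for .05.

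**5. Post-randomisation terms.** No arithmetic applies. Read together, 11.3.1 puts compliance, attrition and instructor ratings in the screen, and 11.3.3.1 admits what the screen finds without restricting it to baseline. Section 11.3.2 names practice amount outright.

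**The case against.** The strongest reply is that the plan is better than the general rule suggests, and several stronger readings do indeed fail.

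- **A reader might infer that all adjustment is chosen after the fact.** It is not. Section 11.3.2 fixes age, sex and education for the primary model. Only the general clause in 7.1.4.3 could add to that list.
- **A reader might extend the fault to the mechanism regression.** Section 11.3.3.2 requires possible effect on outcome as well as imbalance, and it is run across all arms, so it is not an arm comparison.
- **A reader might infer false positives.** The simulation shows none. It did not model discretionary choice among candidates, so it does not clear that risk, but nothing here demonstrates inflation.
- **A reader might take class allocation to make spurious flags the norm.** At ICC .05 the chance of at least one flag in ten would be 73-75%, but that ICC is assumed. At ICC 0 to .01 the per-test rate is 5-6%.
- **A reader might object that the principal investigator holds the allocation.** The same sentence of 7.1.4.3 provides for de-identified codes during analysis, and the choice is made with statistical mentors.

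It may also be said that this is a pilot aimed at estimates and not significance levels. That stands, but it argues for more precise estimates whose definition does not turn on chance.

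What the reply does not touch is that 7.1.4.3, 11.3.1 and 11.3.3.1 state a selection rule. It is not a detail left to a later plan, and an analysis plan that followed it would inherit the fault.

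**Conclusion.** The point holds for the covariates added under 7.1.4.3 and 11.3.3.1, chiefly in the secondary mixed models, and for practice amount in 11.3.2. The harm is threefold: lost precision, an open choice of model, and adjustment for variables that the treatment may have affected.

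The precision loss is about 4 to 5, 12 to 14 and 29 to 30 percentage points of power at r = .3, .5 and .7, taking each of the two runs in turn. This rests on the assumed five candidates, .05 trigger, 0.6 SD difference and individual-level allocation. The bias from post-randomisation adjustment cannot be sized from the protocol. The change should be made; it does not put the sample size or the design in doubt.

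**What to change.** 1. In 7.1.4.3 and 11.3.3.1, replace the trigger with one fixed set for every arm comparison: age, sex, education (already named in 11.3.2) and the baseline value of the outcome.
2. State how baseline enters. In 11.3.3.1 the baseline score is already a response, because time is baseline versus post-intervention, and 11.3.2 models repeated scores. Either use baseline as a covariate with only post-baseline scores as response, or use a repeated-measures model with baseline means constrained equal across arms. It must not appear on both sides.
3. Keep the comparison of baseline characteristics descriptive, with no bearing on the model.
4. Take compliance, attrition, therapist ratings and the meditation practice amount of 11.3.2 out of the arm comparisons. Report them in models labelled exploratory.

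Cost: revised wording, including a clear statement of the model in 11.3.2 and 11.3.3.1, and a few degrees of freedom (four if each covariate enters as a single term). No extra participants or data are needed.

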## 7.2

## Blinding

Individuals who conduct post-treatment (8 week and 3 month) assessments will be blinded to treatment randomization. Since treatment randomization occurs after completion of baseline measures, there is no need for blinding at baseline.

All 3 interventions are active “mindfulness” meditation interventions (i.e. no control or placebo). The only study staff that will be unblinded are the PI and the other therapist who will be delivering the treatments.

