#### 11.4.5.2 Sample size adjustment due to group randomization

Group randomization may require an increase in sample size to maintain power, if the responses of subjects in same group are correlated (intragroup correlation). However, if intra- group correlation = 0, then there is no need for adjustment (Friedman et al., 2010)

In a set of MBCT RCTs that used group randomization procedures and multilevel modeling analysis, Williams (2008) estimated IGCs for depression related outcomes (BDI, relapse rate). Most IGCs were slightly negative, were all smaller than .01 and none of the IGCs were significantly different than 0. Furthermore, a comparison of results corrected vs uncorrected for IGC yielded no difference. Thus, group randomization does not contribute to inflated IGC because the participants in each cohort are selected at random and do not share any common characteristic. Furthermore, sharing the same treatment group experience does not appear to have any effect on outcome either.

Based on this data, we do not plan on adjusting the sample size because of group randomization. We will check the IGC during preliminary analysis, and add into the model if it greater than 0.

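### The unblinded PI keeps the allocation file and issues the analysis codes, so the codes cannot mask the PI, while some adjustment and missing-data choices are made after looking at the data

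*Protocol*

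**What the plan says.** Section 7.1.4.3, under Procedure, has an independent statistician generate the sequence. Each result is then "communicated to the PI who is one of the co-therapists for each treatment". The same paragraph continues: "The PI will maintain the treatment location information in a password-protected electronic file, and provide de-identified codes to signify different treatments during analysis". I read the word location there as allocation. Section 7.2 confirms the PI's status: "The only study staff that will be unblinded are the PI and the other therapist who will be delivering the treatments".

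On the analysis, section 11.3.2 justifies multilevel modelling partly because it "fits my training goals of advanced statistical analysis skills for treatment research". Section 11.3.3.2 says of multiple regression that "it also fits my training goal of increasing multivariate statistical knowledge".

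On open choices, section 7.1.4.3 says baseline differences will be assessed "and if present, incorporated into analysis plan under the guidance of statistical mentors". Section 11.3.3.1 says "variables identified in preliminary analysis will be added to the model as predictor variables or covariates". Section 11.6 says that several ways of handling missing data will be explored if attrition or missingness differs materially between groups.

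On custody, the Masking paragraph of section 7.1.4.3 gives the recording and communication of each allocation to an independent RA without patient contact. The Procedure paragraph that follows gives the same step to the statistician.

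**The concern.** Replacing arm names by codes at analysis has no evident purpose except masking. A code masks only someone who does not hold its key. Here the key holder is told every allocation, helps deliver all three treatments and appears to direct the analysis. Creating the two new modules is also an aim of that person's own award (section 2.2), so the PI is not a neutral party.

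This matters because some modelling choices follow inspection of the data. If they are made with the arms known, they can lean towards an arm without anyone intending it. Blinding the assessors (section 7.2) does not address this. Model choice affects every endpoint, including the self-report scales and the laboratory measures.

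**Working it through.** The plan states no figure on this point, so the check is mainly of the text.

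**1. Does the PI know the arms?** Yes: the PI is told each result, is a co-therapist for each treatment (7.1.4.3) and is listed as unblinded (7.2).

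**2. Does the PI direct the analysis?** Probably. Sections 11.3.2 and 11.3.3.2 give the choice of method in the first person and as a training goal. Neither says who will fit the models. No masked analyst is named.

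**3. Which choices are open?**

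| Choice | Section | Status |
|---|---|---|
| Covariates in the primary model | 11.3.2 | Listed: practice amount, age, sex, education |
| Baseline imbalance | 7.1.4.3, 11.3.3.2 | Decided after looking at the data |
| Covariates in the secondary models | 11.3.3.1 | Decided after preliminary analysis |
| Class (intragroup correlation) term | 11.4.5.2 | Data-dependent but a stated rule: "We will check the IGC during preliminary analysis, and add into the model if it greater than 0" |
| Missing-data methods | 11.6 | Intention-to-treat fixed; alternatives explored, mainly as a sensitivity check |

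The second, third and fifth rows leave room for choice.

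**4. Where would coding fail in any case?**
- Section 11.3.3.1 defines the emotion-regulation outcome by arm: the matching practice for FA and OM, the average of both for MBCT. Whoever derives it must know the arm.
- Section 11.3.1 needs instructor competence and ratings.
- Section 5.2 expects 9-12 classes of varying size. A co-therapist could recognise a class from its size.
- Section 7.3 has its first-person author, evidently the PI, reviewing assessment results weekly.

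**5. How large could the effect be?** This is an illustration under assumptions that the protocol does not supply. Suppose k defensible models give test statistics z1 to zk. Each is standard normal when the arms do not differ, with common correlation r. The model most favourable to one known arm is reported.

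- False claim for that arm: P(max z > 1.96). With one model this is 0.025.
- k = 2, r = 0.8: 2 × 0.025 − P(both > 1.96) = 0.050 − 0.011 = 0.039.
- k = 4, r = 0.8, by simulation: 0.057.
- False claims against that arm need every statistic below −1.96: 0.011 (k = 2) and 0.005 (k = 4).
- Total two-sided error: 0.039 + 0.011 = 0.050 and 0.057 + 0.005 = 0.062.

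The same simulation with r = 0.7 gives false claims for the arm of 0.042 (k = 2) and 0.065 (k = 4); with r = 0.9 it gives 0.035 and 0.047.

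**The case against.** The strongest reply has four parts.

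*The PI may not be the analyst.* Providing codes can naturally mean giving them to someone else. Section 7.1.4.1 mentions biostatisticians, and 7.1.4.3 mentions the guidance of statistical mentors. A separate analyst given only codes could be masked for most outcomes. This stands in part. A reader might infer that the PI runs every analysis and that the codes protect nobody, but the text does not establish either. It does establish that the codes cannot mask the PI and that no masked analyst is named. Guidance from mentors is not masking. A reader might also infer that the PI teaches every class alone; the text says co-therapist for each treatment.

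*The open choices are few.* This also stands in part. The primary covariates are listed, the class term follows a rule, and section 11.6 is mainly a sensitivity check. What remains is not merely detail deferred to a statistical analysis plan: the protocol itself says these decisions follow inspection of the data.

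*The harm is easily overstated.* A reader might attribute to key custody the full inflation from picking the best of several models in either direction. At correlation 0.8 that is 7.8% for 2 models and 11.4% for 4. Such selection needs no key, because an analyst with scrambled codes could do the same. Only the directional part in the working belongs to this point.

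*This is a pilot.* Sections 11.1 and 11.4.1 put estimation ahead of significance, and 11.2 predicts no significant clinical difference. That lowers the weight of any error rate. It does not remove the issue, because choosing models with the arms known can bias the estimates that are meant to inform the larger trial.

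**Conclusion.** The point holds in limited form. The analysis codes cannot mask the PI, who appears to direct the analysis. Adjustment for baseline imbalance, secondary-model covariates and alternative missing-data methods can therefore be chosen with the arms known. That the PI directs the analysis is an inference from first-person wording.

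The size is modest. Under the assumed correlation of 0.8 and 2 to 4 candidate models, false claims for a favoured arm rise from 2.5% to about 4-6%, while total two-sided error stays at 5.0-6.2%. These figures show what would follow if the favourable model were picked; they do not predict that it will be. The conflict between the RA and the statistician in section 7.1.4.3 is clerical but plain. Nothing here impugns the blinding of the assessors as stated in section 7.2.

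**What to change.** 1. In section 7.1.4.3, have the independent statistician who generates the sequence keep the analysis key and issue the arm codes.
2. Have the same statistician derive the arm-dependent emotion-regulation variable (11.3.3.1) and supply the instructor-rating checks (11.3.1), so that neither requires opening the key.
3. Fix, date and file the covariates, the class term and the missing-data method before anyone directing the analysis sees outcome data by arm. Release the key after that. Given the weekly review in section 7.3, this means filing before post-treatment results are reviewed; if some have been reviewed already, the filing should say so.
4. Name who runs the analyses.
5. Reconcile the RA and statistician sentences in section 7.1.4.3 so that one role records and communicates allocation.

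The cost is a short protocol change, modest time from a statistician already involved, and later access to arm labels for the PI. With about 9-12 classes the PI's masking will be imperfect whoever holds the key, so the dated choices in item 3 are the main protection.
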